### Data collection

Most outcome variables are measured using self-report questionnaires. At the intake appointment with the research assistant, after informed consent, the sick-listed worker fills in the baseline questionnaire. All participants are followed one year with measurements, i.e. questionnaires, at 3, 6, 9 and 12 months after baseline. These questionnaires are sent by postal mail. If the received questionnaire is incomplete or if anything is unclear, the researcher or research assistant contacts the participant to clarify and, if possible, to complete the questionnaire. Data on sickness benefit are registered by the SSA and are acquired from the SSA database after one-year follow-up. These data are checked with information regarding sickness benefit as registered by the insurance physician of the SSA in the medical file of the sick-listed worker, and the self-reported information in the questionnaires. Data regarding diagnosis and occupational health care interventions are obtained from the SSA database and medical file of the worker at the SSA. Data regarding RTW are obtained from both the SSA database, including the workers' file, and the self-report questionnaires.

### Prognostic measures

At baseline information is gathered regarding demographic variables, such as gender, age, and level of education. Also, information regarding last work, e.g. type of previous work and number of working hours, and the work status (working or not working) directly prior to the baseline measurement is collected. This is partly based on findings in the international literature [47-49], indicating that the work status before sickness absence is a prognostic factor for the duration of sick leave and work disability.

### Cost-benefit evaluation

Cost-benefit is evaluated from the insurer's perspective. Direct and indirect costs are measured with data from the SSA database and the worker's files, as mentioned above. Direct costs are calculated from the amount of paid occupational health care interventions by the SSA. Indirect costs are calculated from the (additional) costs of paid sickness benefit.

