### The participatory RTW program

The aim of the new RTW program is to make a consensus-based RTW implementation plan. The three main stakeholders in this intervention are: the sick-listed worker himself/herself, the labour expert of the SSA who guides the worker with regard to vocational rehabilitation, and an independent RTW coordinator. The program starts with identifying obstacles for RTW, followed by a brainstorm session in which the sick-listed worker and the labour expert formulate solutions/possibilities for suitable (therapeutic) work. This process results in the making of a consensus-based RTW implementation plan. The RTW coordinator has a key role[35], not in the role of RTW expert, but he/she has to stimulate active involvement of both the sick-listed worker and the labour expert during the whole process and guide them towards consensus. In this study the RTW coordinator is an employee of the SSA with good process guiding skills, an independent position, and sufficient knowledge and experience regarding (vocational) rehabilitation. To guarantee the independence of the RTW coordinator he/she has no other involvement regarding vocational rehabilitation of the sick-listed worker concerned. Furthermore, to create an actual RTW perspective, a vocational rehabilitation agency is contracted to find a (therapeutic) workplace matching with the formulated RTW implementation plan and taking into account the worker's (functional) limitations. For an overview of the steps of the new participatory RTW program and the stakeholders involved, see figure 2.

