### Training of the OHC professionals

Instruction and coaching sessions are held for all involved OHC professionals, i.e. insurance physicians and labour experts of the SSA. They also receive a syllabus with detailed information about the participatory RTW program, the protocol, practical summaries and schemes, and practice material. The RTW coordinators receive an additional training, including a role playing and a practise with anonymous cases and reporting. All professionals are offered personal guidance with the first cases to facilitate applying the program. Next, two follow-up session are held with the professionals to discuss difficulties with working with the program and to practise with cases. Finally, to guarantee that the participatory program is carried out according to the required time-path, each SSA front office forms at least two 'participatory RTW program' teams, i.e. 'STEP-UP teams', consisting of an insurance physician, a labour expert and a RTW coordinator.

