#### - Direct and indirect costs

Direct costs are paid by the SSA for interventions regarding vocational rehabilitation support, e.g. training/education, for interventions aimed at health promotion, e.g. physical therapy (graded activity) and/or psychological help, or interventions aimed at RTW, e.g. searching for a (temporary) workplace by contracting a vocational rehabilitation agency or temporary placement in work with a willing employer and with an ongoing benefit. Information regarding direct costs is collected from the SSA database and the worker's files after one year of follow-up.

Indirect costs are related to costs due to paid sickness benefit for the sick-listed workers with MSD. When looking at sick-listed temporary agency workers and sick-listed unemployed workers, loss of productivity is not part of the indirect costs. When reporting sick the temporary agency workers immediately falls under the SSA for substituted income, i.e. the sickness benefit. The temporary agency replaces the sick-listed temporary agency worker with a healthy worker at the company/workplace concerned with no productivity loss as a result. Therefore, indirect costs with regard to sick-listed temporary agency workers are the sickness benefit costs paid by the SSA. However, this does not apply to unemployed workers. These workers have no work(place), i.e. there is no productivity. As a consequence, being sick-listed does not result in a productivity loss. Another important fact is that an unemployed worker receives an unemployment benefit. After reporting sick with acceptance of the sickness benefit claim by the SSA, the sick-listed unemployed worker receives a sickness benefit instead of an unemployment benefit. However, the amount of these benefits can differ as this is established using different income conditions. As a result, the sickness benefit can be more than the unemployment benefit. From this perspective, the additional benefit costs are considered indirect costs in this study. Data on paid benefits are collected from the SSA database after the one-year follow-up. Cost-benefit evaluation of the new RTW program is part of this study and will be discussed below.

An overview of the outcome measures and the measurement instruments used, including a time path for all measurements, is presented in table 2.

**Table 2 T2:** Overview of measurements and time path

Measurement	Time path				
	**Baseline**	**3 months**	**6 months**	**9 months**	**12 months**

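### The direct-cost rule names no cost item, time record or unit price for the SSA staff who deliver the programme, so its net monetary benefit is probably overstated

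*Protocol article*

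**What the plan says.** The Protocol article takes the payer's view: "Cost-benefit is evaluated from the insurer's perspective". The section on direct and indirect costs defines the first component: "Direct costs are paid by the SSA for interventions regarding vocational rehabilitation support, e.g. training/education, for interventions aimed at health promotion". It then adds a third category, interventions aimed at RTW, with the examples "searching for a (temporary) workplace by contracting a vocational rehabilitation agency or temporary placement in work with a willing employer". The source is also fixed: "Information regarding direct costs is collected from the SSA database and the worker's files after one year of follow-up". The Cost-benefit evaluation section condenses this into one rule: "Direct costs are calculated from the amount of paid occupational health care interventions by the SSA".

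On delivery, the section on the participatory programme states: "In this study the RTW coordinator is an employee of the SSA". The background section on the Dutch social security system places the labour expert and the insurance physician in the SSA team as well. The training section describes sessions for physicians and labour experts and continues: "The RTW coordinators receive an additional training". Under Statistical analyses, costs are computed per participant and feed a mean net monetary benefit against usual care.

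**The concern.** The insurer whose costs are being counted also employs the people who run the core of the programme. A rule built on amounts paid for interventions picks up what the SSA buys in, such as the agency. It does not obviously pick up what the SSA produces with its own salaried staff. That staff time is a real cost from the chosen perspective, and most of it exists only in the intervention arm. If it is left out, the programme is charged for its outside component but not for its inside one, and the comparison with usual care looks better than it should.

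The net monetary benefit is not the primary outcome. It is, however, the economic summary of a programme that the Discussion says may enter usual care if results are positive.

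**Working it through.** **No figure to reproduce.** The article states no staff hours, hourly rate, training cost or daily benefit. The check is therefore a comparison of sections, followed by an illustration on assumed inputs.

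**Step 1: new programme elements against the cost description.**

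| New element (Blinding section) | Delivered by | Named as a direct cost? |
|---|---|---|
| Combined consult, physician and labour expert | SSA staff | No |
| RTW coordinator meetings | SSA staff | No |
| Agency contracted to find a workplace | Outside agency | Yes |

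The programme sections show what the second row involves. The coordinator plans the meetings, interviews the worker and the labour expert separately, leads the brainstorm session, helps draw up the plan, writes a report, contracts the agency, telephones six weeks later and writes a final report. The labour expert adds a consult, an interview, the session and the plan.

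**Step 2: could another data stream supply the time?** The process evaluation covers applicability, compliance, satisfaction and barriers. Its standardised schemes cover obstacles, solutions and the plan. The compliance section asks which interventions were applied. None is said to record time, although costs are needed for each participant.

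**Step 3: direction.** If staff time is left out of both arms, the net monetary benefit is overstated by

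(coordinator cost + additional labour expert cost) − (cost of routine SSA contacts saved by a shorter benefit period).

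The first bracket arises in the intervention arm. The second exists because SSA care ends when the benefit ends. At equal hourly rates, the error favours the programme unless it saves more routine contact time than it consumes.

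**Step 4: illustration, all euro and hour inputs assumed.** Staff cost = hours × rate:

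- low: 4 × 40 = EUR 160
- middle: 8 × 60 = EUR 480
- high: 15 × 80 = EUR 1,200

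Saving = 27 days × daily benefit. The 27 days is the article's figure for the earlier programme in employees with low back pain. The daily amounts are assumed: 27 × 10 = 270, 27 × 30 = 810, 27 × 60 = 1,620. The low daily value is included because for unemployed workers only the excess of sickness benefit over unemployment benefit counts.

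| Saving minus staff cost (EUR) | 10 per day | 30 per day | 60 per day |
|---|---|---|---|
| Low, 160 | +110 | +650 | +1,460 |
| Middle, 480 | −210 | +330 | +1,140 |
| High, 1,200 | −930 | −390 | +420 |

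Agency costs, other paid interventions and any saved routine contacts are not included. If training were spread over the 80 intervention participants, an assumed EUR 20,000 would add 20,000 / 80 = EUR 250 each, and EUR 50,000 would add 50,000 / 80 = EUR 625. The table shows only that the item could matter. It does not estimate its size.

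**The case against.** The strongest reply is that the article excludes nothing. The cost categories are illustrated by open lists, and the programme is plainly an intervention aimed at RTW. The background section uses the term occupational health care interventions for in-house SSA work such as consulting hours and RTW advice, so the same term in the costing rule can be read to include coordinator and labour expert work. Contacts can partly be traced through reports and files, and unit prices are detail that a design article may leave to a fuller document.

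Much of this stands. A reader might infer that the programme's own delivery cost is definitely dropped and that the result is always biased in its favour. The article does not support that. The broader reading is open, usual care also consumes physician and labour expert time, and a shorter benefit period could save some of it. Training is a set-up cost whose inclusion is an analytic choice, so its absence is not in itself a bias.

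What does not stand is the claim that this is only missing detail. The article states both the scope and the source of direct costs. The rule ties them to amounts paid, and the source is files consulted after a year. Even on the broad reading, nothing named would yield the coordinator's hours or their price.

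**Conclusion.** The point holds in conditional form. As the rule is most naturally read, the time of the SSA-employed coordinator and the additional labour expert time are not counted. They are costs to the insurer and fall mainly on the intervention arm, so the net monetary benefit is probably overstated. This rests on two assumptions: that the amount paid means payments for interventions and not salaries, and that the programme uses more staff time than it saves. The size is unknown. The assumed range of EUR 160 to 1,200 per intervention participant, before training, is enough to change the sign in some of the scenarios shown, but that depends entirely on the inputs. The primary outcome is unaffected.

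**What to change.** In the sections on direct and indirect costs and on cost-benefit evaluation, define direct costs as paid interventions plus SSA staff time spent guiding the worker. Then:

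- Record coordinator and labour expert time per worker prospectively on the programme reports.
- In both arms, count insurance physician and labour expert contacts from the SSA files at a standard time per contact, so that only the difference between arms matters. Do not count again any contact already timed on a programme report.
- Value all time at the SSA's internal hourly rate and name that source.
- Show training as a separate line or a sensitivity analysis.
- Compute direct costs, total costs and net monetary benefit on this basis.

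The cost is a time field on the coordinator's reports and some file extraction. The article describes no time form for usual care, which is why the control arm relies on contact counts. The net monetary benefit will probably come out somewhat less favourable.

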### Process evaluation

After implementation a process evaluation is conducted among the participants in the intervention group. Three months after inclusion a questionnaire is sent to the worker, the insurance physician, the labour expert, the RTW coordinator and the case-manager of the contracted vocational rehabilitation agency. For the participants, the process evaluation questions are included in the 3-months questionnaire and sent by postal mail. Questions are asked regarding applicability, compliance, satisfaction and barriers regarding (implementation of) the new RTW program in practice. Patient satisfaction is measured using the Patient Satisfaction with Occupational Health Services Questionnaire (PSOHQ)[50]. In addition, when all participants in the intervention group have had the opportunity to receive the new RTW program, i.e. 3 months after inclusion of the last participant, focus group meetings are held among the staff, management and involved occupational health care professionals of the SSA, and the case-managers of the vocational rehabilitation agencies concerned. The content of these focus groups are based on the principles of context-analysis as proposed by Grol and Wensing[29].

Finally, standardised schemes are used to collect data regarding the identified barriers for RTW, the formulated solutions and the resulting consensus-based RTW implementation plan. The collected data will be analysed qualitatively and quantitatively. In addition, the identified barriers and solutions will be classified using the Ergonomic Abstracts scheme[51,52].

### Sample size

In this study the primary outcome measure is duration of the sickness benefit period. Recurrence of sickness absence (due to the same or related MSD) with an accepted sickness benefit claim within 4 weeks after ending of the previous sickness benefit is considered as belonging to the preceding sickness benefit period. As a starting-point for calculating the sample size we assume that a Hazard Ratio (HR) of 2.0 is the minimal clinical and societal relevant ratio, indicating that temporary agency workers and unemployed workers in the intervention group end their sickness benefit period twice as quickly compared to the workers in the control group. This HR is based on comparable studies on sickness absence and RTW of short-term sick-listed employees[25,46,53-55]. Assuming that the sickness benefit will end for 2/3 of the participants during the one-year follow-up period, and based on a power of (1-β =) 0.80 and a two-sided significance level of 0.05 (α) a sample size of 100 participants (n = 2 × 50) is needed[56]. Since there is a continuous registration of sickness benefit duration by the SSA, a high loss to follow-up with regard to the primary outcome is not expected. However, based on comparable research[57,58] loss to follow-up of 10% is taken into account. This results in 110 participants (n = 2 × 55) to be included in the study. Next, potential clustering of cases assessed by the same insurance physician is taken into account, since the insurance physician plays a key role in acceptance of the sickness benefit claim and the assessment of (sufficient) recovery of functional limitations. For this calculation an ICC of 0.05[25,46] is used and a minimal number of clusters of 10 (i.e. 5 front offices with at least 2 participating insurance physicians at each office). This results in 160 participants (n = 2 × 80) to be enrolled in the study.

### Randomisation procedure

An independent statistician performs the randomisation, using computer-generated randomisation tables. To prevent unequal distribution of relevant prognostic baseline characteristics, before randomisation the sick-listed workers are pre-stratified based on two important prognostic factors, namely type of worker [47-49], i.e. temporary agency worker or unemployed worker, and degree of mental or physical work demands (light or heavy) in last work before current sickness absence[59,60]. Next, block randomisation (using blocks of four allocations) is applied to ensure equal group sizes within each stratum. A separate block randomisation table is generated for each of the five participating front offices of the SSA. Next, the researcher prepares for each stratum opaque sealed envelopes, containing either a referral to the new RTW program group or to the usual care group. After informed consent and completing the baseline questionnaire, the temporary agency worker or unemployed worker is asked to choose one of the two succeeding envelopes of the correct stratum. Then, the worker is asked to open the envelope and write down his/her name and date on the note with the randomisation result.

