### Recruitment of participants

For the recruitment of participants the database of the SSA is used. When reporting sick not only personal data, but also the reason for this, i.e. the health problem, is registered (using codes) in a computerised client record system. Based on a weekly query of this record system, all temporary agency workers and unemployed workers who are sick-listed between one and two weeks due to MSD, and live in the eastern part of the Netherlands receive a letter from the insurance physician of the SSA, on behalf of the researchers. The aim of this letter is to give information about the study and to ask for their participation. In addition, they also receive an information flyer with more details about the study, a screening questionnaire, and a return envelope for the screening questionnaire. The reason for approaching potential participants in the second week of sick leave is the time period in which a RTW action plan has to be made, i.e. 8 weeks after the first day of reporting sick. This is obligated according to the Dutch Improved Gatekeeper Act. Furthermore, it has been shown that early RTW intervention is important to prevent long-term work disability[4,32-34].

Temporary agency workers and unemployed workers who return the questionnaire, and meet the criteria (being temporary agency worker or unemployed worker, and still sick-listed), and indicate that they are willing to participate are contacted by the researchers by telephone. In this telephone call additional information is given about the content of study and the implications of participation. Using the formulated inclusion and exclusion criteria, the eligibility of the worker is checked. If the temporary agency worker or unemployed worker meets all selection criteria and still wants to participate, an intake appointment with the research assistant is planned at one of the UWV front offices. The worker receives a confirmation of this appointment by postal mail, including a detailed information brochure about the study. During the meeting with the research assistant the worker gives informed consent, fills in the baseline questionnaire, and randomisation is performed.

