### Blinding

Since the occupational health care professionals can be involved in guidance of participants of both the intervention group and the usual care group and because the new RTW program contains several new elements compared to usual care, i.e. a combined consult with the insurance physician and the labour expert, meetings with the RTW coordinator, and contracting of a vocational rehabilitation agency for finding a temporary (therapeutic) workplace, the occupational health care professionals cannot be blinded for the allocation. Furthermore, most outcome measures are self-reported, which also makes blinding for the participants not possible. However, the occupational health care professionals and RTW coordinators are not involved in the assessment of the outcomes. Moreover, since all follow-up questionnaires are sent to the participants by postal mail, it is unlikely that direct influence of the researchers or occupational health care professionals will occur.

Since the registration of sickness benefit is done by the SSA, these measurements can be derived from the computerised SSA database. Therefore, bias due to a lack of blinding is prevented for this outcome. Blinding for the secondary outcomes is not possible, because these measurements are derived from self-reported data. After randomisation all participants receive a research code consisting of a unique consecutive number. All data will be put in the computer by a research assistant, using this research code, to guarantee that analyses of the data by the researcher will be blinded.

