### Limitations of the study

A limitation in this study is the absence of blinding of both the sick-listed workers and the occupational health care professionals of the SSA for allocation to the usual care group or intervention group. However, this is not possible due to the nature of the participatory intervention program.

Secondly, because the insurance physician of the SSA has no role in the inclusion of participants, a limitation of this study is the possibility of bias due to self-selection of workers. On the other hand, introduction of bias due to selection of participants by the insurance physician is limited, since the selection procedure is done by the researchers using strict inclusion and exclusion criteria.

A third limitation is the fact that generalizing the results of this study to another context, e.g. other countries, should be done with caution. The new RTW program is specifically tailored to the Dutch context using the Intervention Mapping process [26-28]. Application of this intervention in a different setting should be preceded by tailoring of the program, taking into account the specific characteristics of the social, political and cultural context[26-29,61] in which the program will be implemented and used.

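### The role that screens workers also fills the allocation envelopes, and letting the worker choose between two envelopes defeats the stratum balance that the blocks of four are meant to give

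*Protocol article*

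**What the plan says.** **Sequence and envelopes** (Randomisation procedure). "An independent statistician performs the randomisation, using computer-generated randomisation tables". Workers are stratified by type of worker and by light or heavy work demands, with a separate table for each of five front offices. Within these strata, "block randomisation (using blocks of four allocations) is applied to ensure equal group sizes within each stratum". Then "the researcher prepares for each stratum opaque sealed envelopes". After consent and the baseline questionnaire, the worker is "asked to choose one of the two succeeding envelopes of the correct stratum", opens it, and writes name and date on the note inside. What happens to the other envelope is not stated.

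**Who decides entry.** Under Recruitment of participants, workers who return the screening form and "indicate that they are willing to participate are contacted by the researchers by telephone"; in that call "the eligibility of the worker is checked". Limitations of the study confirms that "the selection procedure is done by the researchers using strict inclusion and exclusion criteria". The intake meeting, where consent, baseline and randomisation take place, is run by a research assistant.

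**Blinding.** Neither professionals nor participants are blinded. Participants get a consecutive research code and an assistant enters the data, "to guarantee that analyses of the data by the researcher will be blinded".

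**The concern.** Concealment protects a trial only if those who decide on entry cannot know what comes next. Whoever fills envelopes from a table has seen the sequence, and here that role belongs to the group that judges eligibility by telephone. Even unintended steering, for instance over whether a worker still counts as sick-listed or when to call back, would make the arms differ in prognosis. The analysis cannot reliably repair that.

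The choice between two envelopes raises a different problem. Permuted blocks balance a stratum only when they are used in order. If the worker may take either of two envelopes, the realised order departs from the generated one and the balance is no longer assured.

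The blinded-analysis claim is a secondary matter. A consecutive code hides who the person is, not which arm they are in. The envelopes are prepared by the researcher. The researcher may also contact participants about incomplete questionnaires (Data collection). Satisfaction is recorded only in the intervention group (Table 2, footnote). Baseline adjustment, clustering correction and co-intervention adjustment are each left to be done if necessary, so it matters whether the analyst knows the arms.

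**Working it through.** **Inputs.** Strata: 2 worker types × 2 demand levels × 5 offices = 20 cells. Planned enrolment is 160 (Sample size), taken as given, so 160 / 20 = 8 workers per cell on average. Block size is 4. Assumptions: cells fill equally, the pick is a fair coin toss, and the unchosen envelope is either returned to the stack or discarded. Both cases are shown.

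**The plan's own aim, envelopes opened in order.** Eight workers use two complete blocks, so every such stratum is exactly 4:4. The stated aim is met.

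**Balance with the choice, unchosen envelope returned.** After 8 draws, nine envelopes have been in play and one is left. The first eight are balanced and the ninth starts a new block. The result is 4:4 unless the ninth was taken and the leftover is of the opposite arm. At the last draw the ninth is taken with probability 1/2. The leftover then comes from an earlier block and is of the opposite arm with probability 1/2. P(unequal) = 1/2 × 1/2 = 25%, always 5:3.

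**Balance with the choice, unchosen envelope discarded.** Eight draws use 16 envelopes, or four blocks, with two allocations from each block. A block's first pair matches with probability 1/3, and the second pair is then the opposite match. If the first pair is mixed, so is the second, and both allocations are coin tosses. Each block therefore contributes a difference of 0 with probability 2/3, or +2 or -2 with probability 1/6 each. Over four blocks:

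P(4:4) = (2/3)^4 + 12 × (2/3)^2 × (1/6)^2 + 6 × (1/6)^4 = 0.198 + 0.148 + 0.005 = 0.350

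So P(unequal) = 65%.

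**Whole trial.** The expected number of unequal strata is 20 × 0.25 = 5 (returned) or 20 × 0.65 = 13 (discarded). In simulation, the 95th percentile of the overall difference between arms was 8 or 20 participants.

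**Predictability** (exact enumeration, 8 workers per stratum):

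| | Opened in order | Choice, returned | Choice, discarded |
|---|---|---|---|
| Certain from past allocations | 33% | 9.1% | 0% |
| Best guess right, from past allocations | 70.8% | 66.5% | 58.3% |
| Both offered envelopes hold the same arm | not applicable | 39.3% | 33.3% |

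The first column by hand: the chance of guessing positions 1 to 4 correctly is 1/2, 2/3, 2/3 and 1, which averages 17/24 = 70.8%. The last row is the share of allocations fixed in advance for someone who knows the envelope contents and which envelopes remain.

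**The case against.** The strongest reply is that the plan has real safeguards. The sequence is independently generated, envelopes are opaque and sealed, a research assistant runs the intake, and the worker opens the envelope after consent and baseline. All of that stands. But these steps follow the researchers' eligibility call, and sealing does not hide contents from the role that filled the envelope.

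A second reply is that the route to steering is not fully shown. The article speaks of the researchers and the researcher, and does not say that one individual does both. Information on last work is collected at the intake, so the full stratum may be unknown when eligibility is judged. Using knowledge of the contents would also mean tracking up to 20 stacks. This stands, and it limits the point to a missing separation of roles.

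Third, for an observer of past allocations the two-envelope choice lowers predictability, from 71% to 58-67%. Correct: its harm is to balance. Unequal strata from a fair pick do not themselves bias the comparison, and unfinished blocks would leave some imbalance anyway.

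On blinding, the holder of the arm key and the handling of masked files may be set out in documents not shown. The primary outcome comes from agency records, so it can be analysed apart from the intervention-only items. That makes the remedy easy, but the article still claims a guarantee that the code alone does not give.

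**Conclusion.** Two points hold. First, the sequence is not concealed from a role that selects participants for an open trial. Second, the choice of envelope contradicts the stated purpose of the blocks: 25% (returned) to 65% (discarded) of 8-worker strata end unequal, against none when envelopes are opened in order. These figures assume equal strata of 8 and a fair pick. Partial foreseeability is 33-39% of allocations for someone who knows the contents and the stack.

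A reader might infer more, and the documents do not support it:

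- **That allocation can be foreseen generally.** Only a minority of draws are fixed in advance, and only for someone with that knowledge.
- **That type I error is inflated by a given amount.** This would need a size of steering that the documents do not supply, so no estimate of bias can be drawn.
- **That the realised sequence cannot be audited.** The named and dated notes leave a partial trail.

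The blinded-analysis point is secondary: the word guarantee claims more than a consecutive code delivers.

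**What to change.** 1. Have the independent statistician already named, or another person outside screening and analysis, prepare sequentially numbered opaque envelopes and keep the list.
2. Delete the choice of two. Open the next numbered envelope in the stratum.
3. Either give the researcher the primary-outcome data with arms labelled A/B, without intervention-only items, until the primary model has been run, or drop the word guarantee.

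The cost is a change of wording and a few hours of the statistician's time, with no added participants or visits.

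There is one trade-off. Opening fixed blocks of four in order restores exact balance in completed blocks, but it returns the guess rate from past allocations to 71%. Varying the block size would lower predictability at the expense of balance. With blocks of 4 or 6 chosen at random with equal probability, the chance that an 8-worker stratum is unequal is the average over the four pairs of first two blocks (4 then 4, 4 then 6, 6 then 4, 6 then 6): 1/4 × (0 + 0.4 + 1/3 + 0.4) = 28%. With about 20 cells of 8, that is no better than the returned-envelope case, so varying the block size is optional.
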